## Abstract

**Background:**

The burden of acute gastroenteritis on children and their families continues to be enormous. Probiotics, defined as viable microbial preparations that have a beneficial effect on the health of the host, represent a rapidly expanding field. Although clinical trials in children with gastroenteritis have been performed, most have significant flaws, and guidelines do not consistently endorse their use.

**Methods/Design:**

PROGUT is a randomized, placebo-controlled, double-blind, five-center, Canadian, emergency department trial. Children aged 3 months to 48 months who present between November 2013 and June 2017 with <72 hours of gastroenteritis symptoms will be assessed for eligibility. A total of 886 children will be randomized (1:1 allocation via an internet based, third party, randomization service) to receive 5 days of a combination probiotic agent (*Lactobacillus rhamnosus* and *L. helveticus*) or placebo. All participants, caregivers, and outcome assessors will be blinded to group assignment. The study includes three key outcomes: 1) clinical - the development of moderate to severe disease following an emergency department (ED) evaluation that employs a validated clinical score (Modified Vesikari Scale); 2) safety - side effect; and 3) mechanism - fecal secretory immunoglobulin A levels.

**Discussion:**

Definitive data are lacking to guide the clinical use of probiotics in children with acute gastroenteritis. Hence, probiotics are rarely prescribed by North American physicians. However, the following current trends obligate an urgent assessment: 1) probiotics are sold as food supplements, and manufacturers can encourage their use while their relevance has yet to be established; 2) North American and European government agencies remain concerned about their value and safety; 3) some institutions are now recommending the routine use of probiotics; and 4) parents of affected children are often providing probiotics. With probiotic consumption increasing in the absence of solid evidence, there is a need to conduct this definitive trial to overcome the limitations of prior work in this field.

**Trial registration:**

ClinicalTrials.gov: NCT01853124; first registered 9 May 2013.

## Background

In the United States each year, there are approximately 179 million episodes of acute gastroenteritis (AGE) [1,2]. Children often suffer from prolonged [3] and severe illness; among hospitalized children, 19% have clinical sepsis, 7% seizures, and 4% require intensive care unit admission [4]. Apart from supportive care, healthcare providers have little to offer to relieve suffering [5].

Probiotics, which are viable microbial preparations that have a beneficial effect on the health of the host, [6] represent a rapidly expanding field. Meta-analyses on their use in children with AGE [7-11] are encouraging; however, they question the relevance of the outcomes evaluated [7,11,12] and advocate for large randomized clinical trials (RCT) [13] in ambulatory pediatric populations [7]. Consequently, in North America, probiotics are rarely used [14-19]. However, current trends obligate an urgent assessment for several reasons. First, probiotics are sold as food supplements, and manufacturers encourage their use through campaigns, making health claims that are not be supported by rigorous research [20-23]. At stake is the $33 billion/year worldwide probiotic market, which is growing at 13% annually [24]. Second, government agencies remain concerned about the value and safety of probiotics [25-27]. Third, some institutions are recommending the routine use of probiotics [28]. Finally, parents are often providing probiotics [16], and consumption is increasing in the absence of evidence.

Prior research suffers from the following shortcomings:

1. Outcome measures used to date have limited clinical meaning. That is, studies have focused on individual symptoms, without consideration of the full picture of the illness [29]. Thus, the significance of the conclusions is questioned [12,30].

2. Quality of studies is inadequate. Most are small, single-center studies [11] that have been conducted by pharmaceutical companies [7]. Many negative studies remain unpublished [31]. Design issues are a concern; only 16% of studies adequately reported the four key methodological assessment parameters [11].

3. Inadequate data are available from research in the relevant patient population. Though 95% or more of children are treated as outpatients [32], only a handful of small studies have focused on outpatients [12]. Hospitalized children are more likely to benefit from probiotics [9,11,33]. Only a single ED study has been performed. In this study, 129 children received a probiotic or placebo agent, and the authors found statistically insignificant trends towards a reduction in stool frequency and duration among those administered a probiotic [34].

4. Knowledge about the *in vivo* mechanism of action in AGE is limited [35,36].

In light of the above considerations, we have obtained funding from the Canadian Institutes for Health Research (CIHR) to conduct the PROGUT (Probiotic Regimen for Outpatient Gastroenteritis Utility of Treatment) trial employing a combination product, Lacidofil™, which contains *Lactobacillus rhamnosus R0011* (95%) and *L. helveticus R0052* (5%).

## Methods/Design

### Hypotheses

In children aged 3 to 48 months of age who present with less than 72 hours of AGE-like symptoms to an ED, the administration of a probiotic agent when compared with a placebo:

1. will result in a significantly lower proportion of children developing moderate to severe disease over the subsequent 2 weeks.

2. will not be associated with a significantly greater occurrence of minor side effects.

3. will be associated with a greater increase in secretory IgA (sIgA).

### Study questions

#### Clinical efficacy

Clinical efficacy will be determined as follows:

1. For previously healthy children, ages 3 to 48 months, who present with less than 72 hours of AGE-like symptoms to an ED, is the probability of developing moderate to severe disease (Modified Vesikari Scale (MVS) score ≥9) following ED evaluation, significantly different in those who receive Lacidofil compared to those who receive placebo?

2. Is there a difference in the (a) mean duration of diarrhea or (b) mean duration of vomiting?

3. Is there a difference in the probability of requiring an unscheduled healthcare provider visit?

#### Side effect profile

In this group of patients, is the proportion that experiences a side effect (for example, bloating, fever, abdominal distention, or rash) significantly different in those who receive Lacidofil compared to placebo?

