### Outcomes

#### Primary outcome (clinical)

The primary outcome is the development of moderate to severe disease in the 2 weeks after the index ED visit as measured by the MVS (Table 1) [44]. The original 20 point Vesikari Score, which has been employed as a dichotomous variable in many clinical studies [45-53], correlates with other meaningful measures such as caregiver anxiety, helplessness, stress, [54] parental worry, behavioral changes, and impact on the parents’ daily activities and distress [55]. However, percent dehydration, an element of the original score, is challenging to quantify due to difficulties in collecting follow-up weights, determining when rehydration has occurred, and the variation related to timing of voiding, stooling, eating, and drinking. Thus, this element is omitted or incorrectly assigned in many studies. The modified score includes an important and easy to obtain outcome that reflects global disease severity - need for unscheduled healthcare provider visits within 2 weeks of the index visit [44]. This is supported by evidence that the utilization of professional medical care correlates with disease severity [54].

**Table 1 T1:** Modified Vesikari Scale

**Points**	**0**	**1**	**2**	**3**
**Diarrhea duration**	0	1 to 96 hours	97 to 120 hours	≥121 hours
**Maximum number of diarrheal stools/24-hour period**	0	1 to 3	4 to 5	≥6
**Vomiting duration (d)**	0	1 to 24 hours	25 to 48 hours	≥49 hours
**Maximum number of vomiting episodes/24-hour period**	0	1	2 to 4	≥5
**Maximum recorded fever**	<37.0˚C R	37.1 to 38.4˚C R	38.5 to 38.9˚C R	≥39.0˚C R
**Future healthcare visit**	0%	-	Primary care	Emergency department
**Treatment**	None	Rehydration	Hospitalization	-

R, rectal.

Follow-up will occur daily until both the diarrhea and vomiting have resolved. On Day 14 each variable is assigned a score for the entire study period (Time 0 to Day 14); each patient gets a single total score for the study. Variables are scored based on the worst 24-hour period or on the total duration of symptoms or are based on the occurrence of an outcome.

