#### Safety

To determine if short course probiotic administration to young children with AGE is associated with an increase in minor side effects, groups will be compared regarding the development of any side effects with particular attention paid to bloating or abdominal distention (grouped for analysis), duration of fever, and buttock rash.

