#### Safety

The proportions of children experiencing any side effect, as reported by the caregivers, will be compared between groups using the Mantel-Haenszel test, stratified by site. The analysis will evaluate the presence/absence of side effects, as an aggregate outcome variable.

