### Safety

The Data Safety Monitoring Committee (DSMC) will meet after 200 and 500 patients to review enrollment, study procedures, form completion, data quality, loss to follow-up, drop-in rate, and interim safety and efficacy results. The analyses will test the hypothesis that the probability of developing moderate to severe AGE in the probiotic arm is equal to that in the placebo arm. Conservative O’Brien-Fleming monitoring boundaries, implemented using the Lan-DeMets alpha-spending function approach, will be used as guidelines for early stopping for safety or efficacy. Based on trends and adverse events, the DSMC may decide to meet sooner than planned using boundaries adjusted accordingly. Because this trial involves children under the age of 6 months, the DSMC has approved a plan to complete an interim safety analysis on the first 20 subjects enrolled under 6 months of age. All serious adverse events will be reported within 24 hours to the DSMC and based on these reports; the DSMC may decide to conduct a safety analysis before the full 20 subjects have been enrolled in this age group. Otherwise, a blinded analysis will be conducted after the 20 subjects <6 months of age have been enrolled. This data will be unblinded if the DSMC deems it necessary to conduct an unblinded interim safety analysis. The results of this analysis will be communicated to Health Canada at the discretion of the DSMC chair should any concerns be identified. The DSMC consists of a biostatistician ([name]-Ottawa), and two physicians with RCT expertise (Drs. [name]-Minnesota and [name] (Chair) -Winnipeg).

An adverse event has been defined as any unfavorable or unintended clinical or other occurrence during the study period that may or may not be the result of participation in the research study.

Expected adverse drug reactions/events include the following, which were deemed to be part of the natural history of the underlying disease process:

1. hospitalization

2. future healthcare provider visit, ED return visit

3. IV rehydration

4. abdominal pain, distension

5. vomiting, diarrhea, fever, flatulence

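### The only named safety test is an any/none side-effect aggregate that counts fever, which is also an efficacy item and an expected disease symptom, so it leans toward finding no excess of side effects

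*Protocol article*

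**What the plan says.** Four parts of the protocol article bear on this.

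- **Study questions, Side effect profile.** The question is a single proportion: "is the proportion that experiences a side effect (for example, bloating, fever, abdominal distention, or rash"). Fever is one of four named examples.
- **Statistical analysis, Safety.** One test is named, with site as the stratification factor: "The proportions of children experiencing any side effect, as reported by the caregivers, will be compared between groups using the Mantel-Haenszel test". The form of the variable is explicit: "The analysis will evaluate the presence/absence of side effects, as an aggregate outcome variable".
- **Outcomes, Table 1 (Modified Vesikari Scale, MVS).** The item "Maximum recorded fever" carries 0 to 3 points of the primary efficacy score.
- **Safety section on monitoring and adverse events.** The list of expected events includes "abdominal pain, distension" and "vomiting, diarrhea, fever, flatulence", "which were deemed to be part of the natural history of the underlying disease process".

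The Safety paragraph under Outcomes adds that the groups will be compared on any side effects "with particular attention paid to bloating or abdominal distention (grouped for analysis), duration of fever, and buttock rash". The second hypothesis is that minor side effects will not be significantly more frequent on probiotic, so a non-significant test supports it.

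**The concern.** A fever after enrollment enters the plan in three roles: as points on the efficacy score, as an expected feature of the illness, and as a side effect. In an any/none variable, a child who is already positive because of fever cannot become more positive by developing bloating or rash. Every child with disease fever is therefore lost as a source of information about the other components.

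Two consequences follow. First, the between-group difference produced by a real rise in bloating or rash shrinks, while the variance of the aggregate usually grows. Second, a product that reduces fever also reduces the side-effect rate, so benefit and harm are netted against each other in one number. Both push toward a non-significant result, which is the result that the safety hypothesis needs. Safety is one of the trial's three key outcomes according to the abstract, and the safety sample-size paragraph says that a difference will be easy to detect without giving any rate.

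**Working it through.** **Plan's own figures.** No figure is given for the safety comparison, so there is none to reproduce. The primary-outcome calculation serves to check the method. For 25% against 15%, two-sided 0.05 and 90% power, the pooled two-proportion formula gives 335 per arm, or 670, as stated. Inflating, 670 / 0.90 / (1 − 0.05 − 0.025)² × 1.02 = 887.5, against 886 stated. Neither figure is in dispute.

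**Inputs for the safety illustration.**
- From the protocol: 886 children randomized 1:1, so 443 per arm; 10% loss to follow-up, so 443 × 0.90 ≈ 399 per arm analysed; two-sided 0.05.
- Assumed, because the protocol gives no rates: bloating or rash rises from b = 10% on placebo to 17% on probiotic; post-enrollment fever occurs in a proportion f, independently of bloating or rash; f is varied from 10% to 70%.

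**Formulas.** Aggregate rate = 1 − (1 − f)(1 − b). With f equal in both arms, the difference is (1 − f) × (0.17 − 0.10) = 0.07(1 − f). Power for detecting an excess is 1 − Φ[(1.96·se₀ − d)/se₁], where d is the difference, se₀ = √[2p̄(1 − p̄)/n] and se₁ = √[(p₁(1 − p₁) + p₂(1 − p₂))/n]. Stratification by site is ignored.

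**Results, n = 399 per arm.**

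| Background fever f | Placebo aggregate | Probiotic aggregate | Difference | Power |
|---|---|---|---|---|
| fever not counted | 10.0% | 17.0% | 7.0 points | 83% |
| 10% | 19.0% | 25.3% | 6.3 | 57% |
| 20% | 28.0% | 33.6% | 5.6 | 40% |
| 30% | 37.0% | 41.9% | 4.9 | 29% |
| 50% | 55.0% | 58.5% | 3.5 | 17% |
| 70% | 73.0% | 75.1% | 2.1 | 10% |

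Worked line for f = 50%: placebo 1 − 0.5 × 0.90 = 0.550; probiotic 1 − 0.5 × 0.83 = 0.585; d = 0.035; se₀ ≈ se₁ ≈ 0.0351; (1.96 × 0.0351 − 0.035)/0.0351 ≈ 0.96; power ≈ 17%.

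**Offsetting by benefit.** Suppose the probiotic also lowers fever from 50% to 45%. Its aggregate becomes 1 − 0.55 × 0.83 = 0.5435, against 0.550 on placebo. The true 7-point rise in bloating or rash then appears as a slightly lower side-effect rate.

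**Other assumed rates.** With all 443 per arm and a component rising from 5% to 10%, power is 81% for the component alone. In an aggregate with background disease symptoms of 30%, 50% and 70%, it is 19%, 11% and 7%.

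**The case against.** The strongest reply is that the Outcomes section already singles out bloating or distention as a group, fever as a duration, and buttock rash. A reader given those component results would see a rise in bloating even if the aggregate were flat. That stands as partial mitigation, and component tables may well be set out in a full protocol or analysis plan that is not shown. It does not remove the point: the analysis section assigns its test to the aggregate, and the study question is posed as one proportion.

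A second reply is that the expected-events list governs what must be reported as an adverse event. Exempting fever from such reporting while comparing its frequency between blinded arms is consistent. This is right. A reader might infer a strict contradiction between that list and the side-effect question, but the documents do not support one. The list matters here only because it shows that the plan itself regards fever and distension as products of the disease.

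Third, a reader might infer that a child who arrives febrile and is still febrile that evening is counted as having a side effect. The article states no such rule. It is silent on onset and worsening, and a condensed article may leave that to the full protocol or the case report form.

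Fourth, fever may matter for tolerability of a live bacterial product: the protocol names concern about bacteremia or septicemia as a ground for unblinding. That is a reason to keep fever as a visible safety comparison, but not to merge it with bloating and rash.

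Randomization balances fever at entry in expectation. It neither restores the lost power nor prevents a treatment effect on fever from masking another effect.

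**Conclusion.** The concern holds in a limited form. As written, the one named safety test mixes an efficacy symptom with possible product effects, and the resulting error favours a conclusion of safety. Under the stated assumptions, power to detect a rise from 10% to 17% falls from about 83% to between 57% and 10% as background fever goes from 10% to 70%. The loss is material even at the low end of that range. The sign reversal needs the further assumption of a fever benefit, here 50% to 45%.

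The size rests on assumed rates and on independence of fever from bloating or rash. It would be tempting to say that disease symptoms swamp the outcome or make up most of the positives; without rates in the protocol, that cannot be asserted. The efficacy overlap concerns fever; distention is called natural history but is not an MVS item. The primary efficacy analysis and the total sample size are unaffected.

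**What to change.** In the side-effect question and in the Safety paragraph of the statistical analysis:

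1. Exclude the symptoms scored in the MVS from the side-effect aggregate: fever, and vomiting or diarrhea if caregivers report them as side effects.
2. Apply the site-stratified Mantel-Haenszel test to the remaining events, and separately to bloating or distention (grouped) and to buttock rash. Report each with a between-group difference and confidence interval, so that the safety conclusion does not rest on non-significance alone.
3. Report fever as its own between-group safety comparison, using the duration measure that the Outcomes section already names, so that it is not lost.
4. Where onset data allow, count events that are new or worse after the first dose.

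The cost is a change of definition, a few more comparisons, and an aggregate that no longer includes fever. Randomization, sample size and the primary analysis do not change.

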#### Mechanism of action

In this group of patients, are fecal sIgA levels 5 days and 4 weeks after the initiation of treatment higher in those who receive Lacidofil compared to those who receive placebo?

### Study design

This a randomized, placebo-controlled, double-blind, five-center, ED-based trial. A total of 886 children will be randomized to receive 5 days of Lacidofil [8 × 10^9^ colony forming units (CFU)/day] or placebo.

### Ethics approval

Site-specific approval has been granted by the local ethics committees at the following study sites: University of Calgary, The Hospital for Sick Children (HSC), Children’s Hospital of Eastern Ontario, Centre Hospitalier Universitaire Ste-Justine, and the IWK Health Centre. A Notice of Authorization has been granted by Health Canada’s Health Product and Food Branch, Biologics and Genetic Therapies Directorate (file #: 9427 - U0206 - 77C).

#### Inclusion criteria

All of the following must be met for inclusion:

1. ≥ 3 watery stools in a 24-hour period [37]

2. duration of vomiting or diarrhea <72 hours

3. age 3 to <48 months

#### Exclusion criteria

Exclusion criteria include:

1. presence of an indwelling vascular access line or structural heart disease [38].

2. taking immunosuppressive therapy, or known history of immunodeficiency [39].

3. hematochezia in the preceding 72 hours, underlying significant chronic gastrointestinal problem or inflammatory bowel disease. This does not including constipation, gastroesophageal reflux or chronic pain.

4. family member with an indwelling vascular access line, on immunosuppressive therapy, or with a known immunodeficiency. This does not include use of short course oral or inhaled steroids.

5. bilious vomiting.

6. supplemental probiotic use in the preceding 2 weeks. The consumption of foods containing probiotics will not result in exclusion.

7. previously enrolled in this trial.

8. daily communication will not be possible while symptomatic.

9. allergy to soy.

10. pre-existing, or known, pancreatic dysfunction or insufficiency [40].

11. oral or gastrointestinal surgery within the preceding 7 days.

### Intervention

Informed consent will be obtained from each participant’s legally authorized guardian prior to enrollment into the study. Once consent is provided, the first dose will be administered in the ED. The sachet’s contents will be sprinkled into 30 mL of oral rehydration solution (ORS). Caregivers will receive instructions on study drug administration, completion of study forms, what and how much fluid to drink, criteria for seeing a health care practitioner or returning to the ED [see Additional file 1] and standardized AGE discharge instructions.

All patients will take one sachet every 12 hours for 5 days, at meal time, even once symptoms have resolved. The dose will be repeated once should vomiting occur within 15 minutes of medication administration. Children who are hospitalized will continue as per study protocol.

### Investigational agents

We have obtained independent analyses to confirm the viable CFU count and microbe identity [see Additional files 2 and 3]. Lacidofil data indicate that a dose of 3 to 6 × 10^9^ CFU/day is effective [41]. A recent pilot trial, which employed low (4 × 10^9^ CFU/day) and high (8 × 10^9^ CFU/day) dose arms, found no side effects with either dose. However, a positive association is postulated to exist between the probiotic dose and clinical benefits [7], with most positive studies employing doses ≥6 × 10^9^ CFU/day [9]. Thus, a dose of 8 × 10^9^ CFU/day is being employed for the current study. The duration of therapy has been selected based on the best available evidence, the recommendations of experts in the field, previous studies, and the typical duration of most episodes of AGE [42].

